### Health-related quality of life

HRQoL is being assessed with the EORTC QLQ-C30, V.3.0, which is validated and available in English and Dutch.^31^ This 30-item HRQoL questionnaire consists of five functional scales (physical, role, cognitive, emotional and social), a global quality of life scale, three symptom scales (fatigue, pain, nausea and vomiting) and a number of single items assessing common symptoms (dyspnoea, loss of appetite, sleep disturbance, constipation and diarrhoea) and perceived financial impact of the disease. After linear transformation, all scales and single-item measures have scores ranging from 0 to 100. A higher score on the functional scales and global QoL means better functioning and HRQoL, whereas a higher score on the symptom scales means more complaints.

### Quality-adjusted life years

QALY is being measured with the EuroQol EQ-5D-5L, which is a descriptive system for the measurement of health.^32^ It measures HRQoL on five dimensions: mobility, self-care, usual activities, pain-discomfort and anxiety-depression. To make the EQ-5D-5L suitable for use in economic evaluations, the health status needs to be valued with a preference-elicitation method.^33^ Both Dutch and English national values were collected and subsequently modelled.^34 35^

### Psychological distress

Psychological distress is being assessed with the Hospital Anxiety and Depression Scale (HADS), which is validated in Dutch and English.^36^ This 14-item instrument measures psychological distress, with seven items each assessing anxiety and depression. The summed total score of the HADS will be used to reflect psychological distress. Higher total scores are indicative of more psychological distress.

### Financial impact

We self-designed a 20-item questionnaire regarding financial barriers to care. The questions were designed based on a literature study of items that are important in health-seeking behaviour but have not been validated. Topics covered are financial barriers to care, financial impact of living with cancer, personal expenses and potential solutions for reducing financial impacts.

### Information provision

Five self-designed questions with multiple items are being asked to identify time points and subjects on which participants would like more information.

### Quality of care

Quality of care is being assessed with the 18-item Patient Satisfaction Questionnaire (PSQ-18),^37^ available in both English and Dutch.^38 39^ This instrument yields scores for each of the seven different subscales: general satisfaction, technical quality, interpersonal manner, communication, financial aspects, time spent with doctor and accessibility and convenience. High scores reflect satisfaction with medical care. In addition, three to five self-designed single items to assess overall satisfaction of care at the primary doctor’s office, hospital and sarcoma centre are being asked.

### Endpoints

The primary endpoint is HRQoL of patients with sarcoma at diagnosis (baseline) as measured with the EORTC QLQ-C30 (global health status). Secondary endpoints are: QALY, psychological distress, stage and tumour size at diagnosis, PFS and OS.

If subgroups are large enough, we will conduct these analyses for different clinically relevant subgroups, such as different histological subtypes, geographical areas, and so on.

### Sample size calculation

We expect a minimum response rate at baseline of 65%, based on rates in other PROFILES studies.^40^ During follow-up, after completion of the first questionnaire, we expect a response rate of 80%. The definition of a long total interval will follow from our statistical analysis (see below), however, if the analysis does not provide a clear cut-off point, we will use the last quartile to define the population with a long total interval.

Using the EORTC QLQ-C30, differences of at least 10 points have been considered as clinically meaningful.^41^ Based on results from our ongoing PROFILES studies, an SD of about 20 points for each scale can be expected. Using an alpha of 0.05, a power of 0.90 and a long diagnostic interval of 25% in the total group of patients with sarcoma, with the expected drop-out, would require 265 patients.^42^ In order to make country-to-country comparisons, we aim to include 265 Dutch and 265 English patients in a time frame of 18 months with a total follow-up of 24 months.

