Change in HRQoL during the follow-up period of 2 years and factors associated with changes in HRQoL will be analysed using repeated measures mixed models. This will be compared between patients with a short and long total interval, using repeated measures analysis of variance, controlling for relevant patient and tumour characteristics, and the patient’s baseline score. Clinically relevant differences will be assessed using Cocks’ method.^41 42^

Other patient-reported outcomes such as QALYs and psychological distress will be analysed in the same way.

Multivariate analyses will be performed to examine associations between total interval length and (1) QALYs, (2) psychological distress, (3) stage at diagnosis and (4) tumour size. These analyses will be corrected for potential confounders including patient and tumour characteristics and healthcare system.

Both unadjusted and adjusted multivariate Cox proportional hazard regression analyses will be used to examine whether a long total interval is associated with PFS or OS.

PFS is defined as the time interval between diagnosis until clinical or radiological progression, as assessed by the treating consultant. OS is defined as the time from diagnosis until death.

Statistical analyses will be performed using IBM SPSS V.25.0; two-sided p values <0.05 will be considered statistically significant.

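### The stated sample-size inputs do not give 265 patients with either response rate in the paragraph; the figure, or the power attached to it, needs restating

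*Protocol article*

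**What the plan says.** All inputs but one are in the protocol article under Sample size calculation.

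- Effect: "differences of at least 10 points have been considered as clinically meaningful". The SD is put at about 20 points for each scale.
- Error rates and split: "Using an alpha of 0.05, a power of 0.90", continuing to "a power of 0.90 and a long diagnostic interval of 25" per cent of the whole sarcoma group. Sidedness comes from Statistical analysis: "two-sided p values <0.05 will be considered statistically significant".
- Response: "We expect a minimum response rate at baseline of 65" per cent and, once the first questionnaire has been completed, "we expect a response rate of 80" per cent.
- Result: the inputs, "with the expected drop-out, would require 265 patients".
- Use of the result: "In order to make country-to-country comparisons, we aim to include 265 Dutch and 265 English patients".

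The Endpoints section sets the primary endpoint as global health status at diagnosis, that is, at baseline. The sample size paragraph does not say which of the two rates is the expected drop-out, nor whether 265 counts patients approached, patients enrolled or questionnaires analysed.

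**The concern.** This is the article's only power statement. A reader who meets a null result will rely on it to judge whether a 10-point difference could have been missed. The sentence presents 265 as following from the inputs beside it. If it does not follow, the reader cannot tell which element gave way: the 0.90 power, the 25% split or the drop-out allowance. The choice of rate matters too, because a follow-up loss cannot reduce the number available for a baseline endpoint.

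An article may leave detail to the full protocol. Here, however, the issue is a printed number that disagrees with the printed inputs, not an omitted detail.

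**Working it through.** **Inputs.** Difference 10, SD 20, two-sided alpha 0.05 (z = 1.960), power 0.90 (z = 1.282), proportion with a long interval p = 0.25.

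**Step 1: analysable patients needed.** For two means with unequal groups,

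N = (z_alpha + z_beta)² × SD² / [difference² × p(1 − p)]

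= (1.960 + 1.282)² × 400 / (100 × 0.1875) ≈ 224.2, so 225.

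In whole groups at 1:3 this is 57 + 171 = 228. A noncentral t calculation also gives 228.

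**Step 2: try to reproduce 265 with the stated rates.** Divide by the proportion responding.

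| Rate applied | From 225 | From 228 |
|---|---|---|
| 80% follow-up response | 225/0.80 = 281.3 | 228/0.80 = 285.0 |
| 65% baseline response | 225/0.65 = 346.2 | 228/0.65 = 350.8 |
| Both (0.65 × 0.80 = 0.52) | 225/0.52 = 432.7 | 228/0.52 = 438.5 |

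None is 265. One-sided testing does not rescue it: at 25:75 it needs 183 to 188 analysable patients, which become 229 to 235 at 80% and 282 to 290 at 65%.

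**Step 3: what drop-out would fit?** 225/265 = 0.849 and 228/265 = 0.860, so a drop-out of 14 to 15%. The article gives no such rate.

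**Step 4: what 265 per country delivers.** Power = Φ(√[N × 0.1875] × 10/20 − 1.960).

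| What 265 counts | N analysed | Power per country | Power with both countries pooled |
|---|---|---|---|
| Baseline questionnaires received | 265 | Φ(3.524 − 1.960) = 0.94 | 0.999 |
| Baseline received, 80% at follow-up | 212 | Φ(3.152 − 1.960) = 0.88 | 0.99 |
| Patients approached, 65% respond | 172 | Φ(2.840 − 1.960) = 0.81 | 0.98 |
| Patients approached, both losses | 138 | 0.72 | 0.95 |

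The t-test values are within 0.01 of the per-country figures (0.940, 0.881, 0.807 and 0.713). The pooled column uses 530 times the same proportion, with the same SD and the same 25:75 split.

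**The case against.** **The design may well meet its target.** The article aims to include 265 per country. It describes questionnaires as following consent (Study design and setting) and the first case report form as completed on inclusion (Case report forms). That points to enrolled participants rather than people invited. The primary endpoint is at baseline, so follow-up loss does not touch it, and 265 baseline questionnaires give 0.94. This stands. A reader might infer from the failed arithmetic that the study does not deliver 0.90 power; the article does not support that. Only the reading in which 265 are approached falls clearly short per country, and no section states that reading.

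**The gap at 80% is small.** The shortfall is 16 to 20 patients per country (281 to 285 less 265). The SD is only said to be about 20, and an SD of 19.3 would give 0.90 with 212 patients. This also stands, and it limits the seriousness. It does not make 265 the result of the stated inputs.

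**The country comparison.** A reader might infer that it is underpowered, because 265 was derived for long versus short interval. The article states no effect or power for comparing countries, so no figure is contradicted. A simple 10-point difference between countries has power of at least 0.986 in all four scenarios above. A country-by-interval interaction of 10 points would be weaker (about 0.70 with 265 per country), but the Statistical analysis section specifies no such test. Similarly, the small effect size mentioned there concerns the choice of cut-off for a long interval and is not a powering target.

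**Where 265 came from.** 172/0.65 = 264.6, and 172 is the total for two equal groups at 0.90 power, or for 25:75 at 0.80 power. It is tempting to conclude that the split or the power was dropped. That is conjecture: the two origins are incompatible with each other, and a different slip (225 × 1.2 = 270) also lands nearby.

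**Conclusion.** The point holds as an error in a stated figure. With the printed inputs and two-sided testing, 0.90 power at 25:75 needs 225 to 228 analysable patients per country, and neither stated rate turns that into 265. The printed figure is about 6 to 7% below the 80% result (265 against 281 to 285) and about 23 to 24% below the 65% result (265 against 346 to 351).

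The consequence is limited. If 265 counts baseline questionnaires, the more natural reading, the primary comparison within each country has about 0.94 power, better than stated, and follow-up comparisons have about 0.88. If 265 counts patients approached, per-country power is about 0.81. Pooled power is at least about 0.95 throughout. All of this assumes a difference of 10, an SD of 20 and a 25:75 split, as the article does. It is a correction to the reporting of the design, of modest severity, and not a reason to recruit more patients.

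**What to change.** Rewrite the sample size paragraph as follows.

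- State that 225 to 228 analysable patients are needed for 0.90 power at a 25:75 split, two-sided.
- State what 265 per country counts.
- If it counts baseline questionnaires received, report about 0.94 power for the baseline primary endpoint and about 0.88 for follow-up comparisons at 80% response (265 × 0.80 = 212).
- If it counts patients approached, report about 0.81 for the baseline endpoint within a country (265 × 0.65 = 172).
- Remove the reference to an unspecified drop-out, or give the rate and the outcome to which it applies. The 80% rate should not be applied to the baseline endpoint.
- Add that the pooled 530 exceed 0.90 power in each of these cases.

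The cost is a few sentences and no additional patients. By 23 March 2020 Dutch recruitment was finished and the UK target was almost reached (section on the impact of COVID-19), so the restatement can use the numbers actually received. A UK total somewhat below 265 would still meet 0.90 as long as 225 to 228 baseline questionnaires are analysable.

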### Statistical analysis

Descriptive statistics (means, SD, median, range, frequencies) will be used to quantify diagnostic intervals and describe the study population.

HRQoL at baseline will be calculated according to the EORTC scoring manual.^43^ Missing items will be imputed according to these guidelines, after which an available case analysis will be performed.

The relationship between total interval length and HRQoL at baseline will be investigated by plotting HRQoL against total interval length as a continuous variable. Linear regression will be used to assess their association. The time point providing a significant difference in HRQoL will be used as a cut-off point for further analysis. If this does not provide a clear cut-off point, logistic regression will be used to assess an association between baseline HRQoL and total interval grouped into suitable categories, such as quartiles. The last quartile will then be used to define the population with a long interval.

Apart from statistical significance, we will look at clinically relevant differences in HRQoL scores as determined by Cocks *et al.*^42^ A small effect size will then be considered as an appropriate value for a cut-off point.

A series of univariate logistic regression analyses will be conducted to assess the relationship between total interval length (grouped by the cut-off point as defined by the previous analysis) and independent variables, such as patient, tumour and healthcare system risk factors. All factors with p<0.1 will then be used in multiple logistic regression analysis (forced entry method) to investigate whether these factors are independently associated with total interval length.

Apart from total interval length, the association of other patient and tumour characteristics (such as self-efficacy, social support, financial difficulties, histology), and HRQoL at baseline will be investigated using univariate logistic regression analysis. Using the forced entry method, multiple logistic regression analysis will then be performed with all factors with p<0.1 to assess what factors are independently associated with baseline HRQoL.

Change in HRQoL during the follow-up period of 2 years and factors associated with changes in HRQoL will be analysed using repeated measures mixed models. This will be compared between patients with a short and long total interval, using repeated measures analysis of variance, controlling for relevant patient and tumour characteristics, and the patient’s baseline score. Clinically relevant differences will be assessed using Cocks’ method.^41 42^

Other patient-reported outcomes such as QALYs and psychological distress will be analysed in the same way.

Multivariate analyses will be performed to examine associations between total interval length and (1) QALYs, (2) psychological distress, (3) stage at diagnosis and (4) tumour size. These analyses will be corrected for potential confounders including patient and tumour characteristics and healthcare system.

Both unadjusted and adjusted multivariate Cox proportional hazard regression analyses will be used to examine whether a long total interval is associated with PFS or OS.

PFS is defined as the time interval between diagnosis until clinical or radiological progression, as assessed by the treating consultant. OS is defined as the time from diagnosis until death.

Statistical analyses will be performed using IBM SPSS V.25.0; two-sided p values <0.05 will be considered statistically significant.

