**Trial registration number:**

NCT03441906.

Strengths and limitations of this studyThe international design allows for comparison of healthcare systems and its influence on total interval length.Multicentre, prospective design allows reliable comparison of sarcoma subgroups to make clinically relevant recommendations to improve total interval.Inclusion of patients at diagnosis minimises recall bias for total interval length.Patients were actively involved in the design of this study and mentioned earlier diagnosis and patient-reported outcomes as research priorities.

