## Methods and analysis

### Study design and setting

We will conduct a longitudinal, prospective, cohort study among adult sarcoma patients, newly diagnosed in one of the participating study centres (five centres in the Netherlands: Radboud University Medical Centre Nijmegen, Erasmus Medical Centre Rotterdam, University Medical Centre Leiden, University Medical Centre Groningen, Netherlands Cancer Institute Amsterdam; three centres in the UK: The Royal Marsden London, Christie Manchester, Royal Orthopaedic Hospital Birmingham, all NHS Foundation Trusts). The study started recruitment at the first centre in the Netherlands in February 2018 and in the UK in October 2018 and is currently recruiting.

After informed consent, patients are being asked to complete questionnaires at five points in time: the first at baseline, preferably before start of treatment or within 4 weeks thereafter, and at 3, 6, 12 and 24 months follow-up (table 1). Baseline questionnaire completion will take about 45 min, follow-up questionnaires will take 20–30 min each.

**Table 1 T1:** Time points and questionnaire items

Item (number of items)	Scale	0 months	3 months	6 months	12 months	24 months
Characteristics						
Sociodemographic (max 20)		X	X	X	X	X
Comorbidity (15)	SCQ	X			X	X
Total interval (max 42)	Own design	X	X	X	X	X
Health literacy (1)	SBSQ	X				
Social support (1)	QLCS	X		X		X
Self-efficacy (10)	GSE	X				
Coping (28)	Brief COPE		X			
Resilience (6)	BRS			X		
Outcomes						
Health-related quality of life (30)	EORTC QLQ-C30 version 3.0	X	X	X	X	X
Quality-adjusted life years (6)	EQ5D5L	X	X	X	X	X
Psychological distress (14)	HADS	X	X	X	X	X
Financial impact (20)	Own design	X	X	X	X	X
Information provision (max 26)	Profiles registry		X			
Quality of care (max 23)	PSQ-18 and 3–5 single items	X	X	X	X	X
Total number of items		194	158	105	113	114

BRS, brief resilience scale; COPE, Coping Orientation to Problems Experienced; EORTC QLQ, European Organisation for Research and Treatment of Cancer Quality of Life Questionnaire; EQ5D5L, European Quality of life 5 Dimensions 5 Levels; GSE, general self-efficacy; HADS, hospital anxiety and depression scale; PSQ, patient satisfaction questionnaire; QLCS, quality of life-cancer survivors; SBSQ, set of brief screening questions; SCQ, self-administered comorbidity questionnaire.

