### Participants

Eligible patients are invited by their treating physician or a member of the research team. Inclusion criteria are: (1) aged ≥18 years; (2) new histological diagnosis of sarcoma as confirmed by a sarcoma histopathologist (according to the International Statistical Classification Of Diseases And Related Health Problems, 10th revision, German Modification (ICD-10-GM) codes C40 and C41 for bone sarcoma and C49 for soft-tissue sarcoma); (3) able to communicate in English or Dutch and to complete questionnaires themselves; (4) mental capacity to provide informed consent and participate in the study (as determined by the healthcare professional) and (5) diagnosed at or referred to one of the participating hospitals. Exclusion criteria are: (1) too ill to complete questionnaires (according to treating physician—patients who experience symptoms are still eligible); (2) desmoid fibromatosis and gastrointestinal stromal tumours due to the different nature of the diseases (ICD-10-GM codes C15-20, C26, C48 and C80).

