### Case report forms

CRFs will be completed at five time points during the study. The first will be completed on inclusion, the following time points coincide with the completion of follow-up questionnaires. The last CRF is also the end-of-study CRF, which can be completed before 24 months if a patient withdraws or deceases. The information collected on the CRF will be stored on a secure CRF database using anonymous study numbers. Data collected includes documentation of eligibility criteria, date of diagnosis, tumour characteristics such as histology, tumour, node and metastasis (TNM) stage, tumour size, treatment regiment, re-occurrence of disease or metastases, reason for withdrawal of the study and time of death, if applicable.

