### Total interval

A 42-item list was self-designed to assess the total interval. Examples of questions are as follows: ‘With which symptom(s), caused by the sarcoma, did you first go to a doctor?’, ‘To which doctor did you first talk about your symptoms?’ and ‘How often did you talk to the following doctors about your symptoms belonging to sarcoma, before you heard you had a sarcoma?’ At follow-up, a few questions are repeated to complete data collection. We will sample survey the reported dates by cross-checking them with the patient’s record. If more than 5% of the cross-checked dates deviates more than 1 month from the registered dates in the medical record, we will cross-check all dates and use the clinical reported dates for statistical analysis.

Health literacy is being assessed by a Dutch adaptation of Chew’s Set of Brief Screening Questions (SBSQ) in a single-item question.^23–25^

Social support is being assessed by one single item: ‘Was the amount of support you received from others sufficient?’ extracted from the Quality of Life-Cancer Survivors questionnaire.^26 27^

Self-efficacy is measured with the General Self-Efficacy scale (GSE).^28^ This 10-item scale assesses a general sense of perceived self-efficacy with the aim to predict coping with daily hassles as well as adaptation after experiencing a stressful life event. Self-efficacy is the belief that one can perform a novel or difficult task, or cope with adversity. Perceived self-efficacy facilitates goal-setting, effort investment, persistence in face of barriers and recovery from setbacks. Responses are made on a 4-point scale. A higher final composite score correlates with higher perceived self-efficacy.

Coping is assessed in the 3-month questionnaire with the help of the brief Coping Orientation to Problems Experienced (COPE).^29^ Coping is about emotional and mental reactions, which enable people to activate sources of help needed to cope with stress and problems. This 28-item scale measures 14 positive and negative styles of coping on a 5-point Likert-scale.

Resilience is measured in the 6-month questionnaire using the Brief Resilience Scale (BRS).^30^ Resilience is a skill that helps people recover from a life event. People with high (perceived) resilience can move on faster after a setback. The BRS is a 6-item scale with a 5-point Likert scale.

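### Symptom-onset date and the primary HRQoL score come from the same patient in one post-diagnosis questionnaire, and the date check looks only at the size of errors, so HRQoL-related recall error could contribute to the primary slope unseen

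*Protocol article*

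**What the plan says.** - **Exposure.** The section Total interval states: "A 42-item list was self-designed to assess the total interval". Table 1 (Study design and setting) places these items at 0 months, with some repeated at follow-up.
- **Outcome.** The primary endpoint (Endpoints) is QLQ-C30 global health status at baseline. Table 1 places the QLQ-C30 in the same 0-month questionnaire.
- **Timing.** Eligibility requires a "new histological diagnosis of sarcoma as confirmed by a sarcoma histopathologist" (Participants), so the diagnosis precedes the questionnaire. That questionnaire is "the first at baseline, preferably before start of treatment or within 4 weeks thereafter" (Study design and setting).
- **Analysis.** Statistical analysis: "The relationship between total interval length and HRQoL at baseline will be investigated by plotting HRQoL against total interval length" as a continuous variable, then linear regression. The time point giving a significant difference becomes the cut-off for later analyses, with the last quartile as fallback.
- **Safeguards.** The strengths box states: "Inclusion of patients at diagnosis minimises recall bias for total interval length". The section Total interval cross-checks a sample of reported dates against the record. The trigger reads "If more than 5% of the cross-checked dates deviates more than 1 month from the registered dates in the medical record"; all dates are then checked and the clinical ones used. Separately, the CRF holds the end of the interval: "Data collected includes documentation of eligibility criteria, date of diagnosis, tumour characteristics".

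**The concern.** A patient who feels worse at diagnosis may search memory harder and place the first symptom earlier. That error depends on the outcome, so it does not simply dilute the slope as random error would. It can produce a slope where none exists, in the direction the study expects (longer interval, lower HRQoL).

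Asking at diagnosis shortens the recall period and so reduces the amount of error. It does not stop what remains from varying with current health. The date check does not address this either: it is a count of absolute deviations, and the same count arises whether the errors are unrelated to HRQoL or all lie on one side among the most unwell patients.

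At stake is what a significant slope means, and where the cut-off falls if it is taken from that slope. The exposed component is mainly the first-symptom date, since the CRF also records the date of diagnosis.

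**Working it through.** The plan gives no figure for recall error, so there is none to reproduce. The check asks how small an HRQoL-related shift could matter, and whether the date rule would notice it.

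**Inputs from the protocol article.** HRQoL SD 20 points; n = 265 per country, 530 in all (taken here as the numbers analysed); two-sided 0.05; trigger at more than 5% of checked dates more than 1 month off.

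**Assumptions (not in the article).** No true association. True interval T is lognormal with median 3 or 6 months and log-SD σ of 0.8 or 1.3. z is standardised HRQoL, independent of T. There is no other recall error and the record holds the true date.

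**Step 1: correlation needed for significance.** About 0.121 at n=265 and 0.085 at n=530.

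**Step 2: shift of 0.5 month per 20 points.** Reported interval = T − 0.5z.
- SD(T) = median × exp(σ²/2) × √(exp(σ²) − 1).
- Induced correlation r = 0.5/√(SD(T)² + 0.25).
- With d = r√(n−2)/√(1−r²), false-positive rate ≈ Φ(d − 1.96) + Φ(−d − 1.96).

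| Median, σ | SD(T), months | r | n=265 | n=530 |
|---|---|---|---|---|
| 3, 0.8 | 3.91 | 0.127 | 54% | 84% |
| 6, 0.8 | 7.82 | 0.064 | 18% | 31% |
| 6, 1.3 | 29.4 | 0.017 | 6% | 7% |

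Simulation over the same range gives 6-56% (n=265) and 7-84% (n=530).

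Share of first-symptom dates flagged: P(|0.5z| > 1) = P(|z| > 2) = 4.6%. This lies just under 5% even if the rule is applied to that date alone.

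**Step 3: interval 5% longer per 20 points lower.** Reported interval = T × 1.05^(−z). With a = ln 1.05 = 0.0488, r = a/√(exp(σ² + a²) − 1).
- σ = 0.8: r = 0.051, giving about 13% (n=265) and 22% (n=530).
- σ = 1.3: r = 0.023, giving about 7% and 8%.

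Simulation gives 8-15% and 8-24%.

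The flagged share is P(T × |1.05^(−z) − 1| > 1). At a 6-month median this is 6-13% of first-symptom dates, over the limit if that date is judged alone. If it were one of four pooled dates and the other three agreed, the share would be 6/4 = 1.5% to 13/4 = 3.3%, under the limit. The article does not say how many dates are checked or whether they are pooled.

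**Step 4: ordinary recall error added.** Adding random error of 10% of the interval to Step 3 (6-month median) puts 22-28% of first-symptom dates over 1 month. Divided by four, that is about 5.5-6.9% of pooled dates, which trips the rule.

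**Step 5: size on the HRQoL scale.** The spurious difference between the top quartile and the rest is about 1-4 points for the shifts in Steps 2 and 3. The Sample size calculation treats 10 points as clinically meaningful.

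**The case against.** A reader might infer that the check would pass and that the primary association is therefore likely to be an artefact. The documents do not support that.

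- **The rule has force.** If the record's dates are independent of the patient, a 10% stretch per 20 points flags 6-33% of first-symptom dates (medians 3-9 months, log-SD 0.8 or 1.1). Step 4 shows that modest random error can also trip the rule, even pooled. Clinical dates then replace the reported ones.
- **The mechanism is assumed.** No figure in the article gives the size of HRQoL-related recall error, and any study relying on patient-reported onset shares this limit. With long, widely spread intervals on the raw scale the inflation is slight.
- **The spurious difference is small.** It is well below 10 points, and Statistical analysis looks at clinical relevance as well as significance.

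All three points stand, and they limit the concern. The third is only a partial answer, because the same section accepts a small effect size for choosing the cut-off.

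Two further inferences fail. Not every later long/short comparison inherits the problem in the same way: stage, tumour size, PFS and OS are not self-reported. Nor is the strengths statement wrong: it claims that recall bias is minimised, not removed.

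It could also be said that an extra sensitivity analysis belongs in the full protocol or SAP. That is fair for analysis detail. But the article does state the date rule and its trigger, and as stated the rule cannot show whether errors go with HRQoL.

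**Conclusion.** The point holds in a limited form. Exposure and primary outcome share a respondent, a questionnaire and a time point after diagnosis, and the stated check measures only the size of date errors. HRQoL-related recall error could therefore stay under the trigger and contribute to the slope.

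How much is unknown. Under the assumptions above, the false-positive rate ranges from near nominal (6-8%) with long, widely spread intervals to 56% (n=265) or 84% (n=530) for a half-month shift with short ones. The apparent effect is about 1-4 points. These are conditional illustrations, not an estimate of bias in this cohort. They justify a cheap diagnostic and a sensitivity analysis; they do not justify discounting the primary result in advance.

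**What to change.** 1. **Use the cross-check to look at direction.** In the checked patients, compute the signed difference (reported minus recorded) separately for each date type. Apply the 5% count to the first-symptom date on its own as well as pooled. Regress the signed difference on baseline global health status and report the slope with its confidence interval. For the first-symptom date, a positive slope means that patients with lower HRQoL date onset earlier. If the slope is clearly non-zero, use clinical dates as under the existing trigger. Since the size of the checked sample is not stated, a wide interval around zero should not be read as reassurance.

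2. **Add a sensitivity analysis whether or not the trigger fires.** Repeat the primary regression (a) with record-based dates where available and (b) with the record-dated diagnostic interval. Report estimates and confidence intervals beside the main result, and state that the diagnostic interval omits the patient interval and is a different exposure. Do not use agreement in direction as a test of robustness: with no association, the signs agree by chance about half the time.

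**Cost.** A little more analysis of data the plan already provides for, with no new patients or questionnaires. The sensitivity analysis will have less power than the main one. Both steps are weaker where the record's onset date was itself taken from the patient's account, and the article does not say how often that is so.
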